**Table 4. Event Rate Differences Between Groups**

|  | **0.07 vs 0.05** | | | **0.10 vs 0.05** | | | **0.15 vs 0.05** | | | **0.20 vs. 0.05** | | |
| --- | --- | --- | --- | --- | --- | --- | --- | --- | --- | --- | --- | --- |
| **Power** | **Total  N** | **COVID**  **(+)** | **COVID**  **(-)** | **Total N** | **COVID**  **(+)** | **COVID**  **(-)** | **Total  N** | **COVID**  **(+)** | **COVID**  **(-)** | **Total N** | **COVID**  **(+)** | **COVID**  **(-)** |
| 0.9 | 8012 | 6009 | 2003 | 1592 | 1194 | 398 | 516 | 387 | 129 | 180 | 135 | 45 |
| 0.8 | 6076 | 4557 | 1519 | 1224 | 918 | 306 | 404 | 303 | 101 | 144 | 108 | 36 |
| 0.7 | 4844 | 3633 | 1211 | 988 | 741 | 247 | 332 | 249 | 83 | 120 | 90 | 30 |
| 0.6 | 3904 | 2928 | 976 | 808 | 606 | 202 | 272 | 204 | 68 | 100 | 75 | 25 |

## 3.9. Statistical methods

### 3.9.1. Outcomes

Statistical analyses will describe disease course and outcomes, including the characterization of specific symptoms and duration of symptoms, health care utilization (emergency department, hospitalization, post-acute care) with clinical (morbidity/mortality) and patient-reported health status outcomes as well as recovery (early and late disease sequelae). Baseline and demographic characteristics will be summarized by descriptive summaries (e.g., means and standard deviations for continuous variables such as age and percentages for categorical variables such as gender, medians, and quartiles for skewed data). Analyses will:

- Compare health status at baseline and follow-up between persons in the same age group who test SARS-CoV-2 positive and negative at initial test.
- Characterize health care utilization (ambulatory and ED visits, hospitalizations, post-acute care, telehealth visits) among SARS-CoV-2 positive participants by age and compare these to SARS-CoV-2 negative participants.
- Characterize and compare health outcomes by age and SARS-CoV-2 status: emergency or ambulatory care, admission to hospital); ICU-free survival;^16^ hospital-free survival; and subsequent patient-reported health status (cognition; physical health; mental health; and return to work).

We will use statistical modeling to estimate the association between key covariates and outcomes, including evaluating interactions by age. We plan to use survival analysis techniques to analyze time to outcome events, logistic regression for binary outcomes (e.g., hospitalization versus no hospitalization), Poisson or Cox regression for count data (e.g., number of hospitalizations over time), and linear regression models for continuous outcomes (e.g., PROMIS-29). Multiple imputation will be considered to handle missing covariate and outcome data in these analyses [[43]](https://www.spiritprotocol.com/api/docx/https://paperpile.com/c/nKRweq/3dpny). Chained equations will be used to impute each variable with missing data. Sensitivity analyses will be conducted using missing categories for covariates and including only people with non-missing outcome information.

We will use statistical analyses to address the risk of ME/CFS and other health conditions in those with versus without SARS-CoV-2 infection as risk difference or risk ratios or odds ratios, as appropriate. We will also adjust for additional patient-level factors of interest, including age, sex, race/ethnicity, income, and presence of specific underlying conditions such as hypertension and diabetes. We anticipate that as more is learned about the clinical courses of persons with symptomatic SARS-CoV-2 infection, additional covariates of interest available from electronic record data will be assessed for their association with adverse outcomes.

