## 3.4. Interventions

### 3.4.1. Intervention description

This is a prospective, observational study without an intervention.

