## 3.8. Sample size

Our target enrollment is 3,600 people with SARS-CoV-2 infection confirmed by a positive SARS-CoV-2 viral test (i.e., nucleic acid amplification test or antigen test) and 1,200 people with a negative SARS-CoV-2 viral test. We expect that the age distribution of enrolled subjects will represent that of patients tested in each site. Four of the sites (Yale, Jefferson, Rush and UW) draw on smaller catchment populations so have planned enrollment of 400 subjects per site (300 individuals with SARS-CoV-2 and 100 individuals without SARS-CoV-2). Four sites (UT Southwestern, UT Houston, University of California, San Francisco, and University of California, Los Angeles) have larger catchment populations so have planned enrollment of 800 subjects per site (600 individuals with SARS-CoV-2 and 200 individuals without SARS-CoV-2).

We estimated the power to detect relative differences in outcome rates between those who are symptomatic and test positive for SARS-CoV-2 as compared to those who are symptomatic but test negative for SARS-CoV-2. These power calculations are agnostic to the outcome of interest but based on the aim to examine relative differences in long-term outcomes between individuals with and without SARS-CoV-2 based on and between age strata. For comparison of ME/CFS incidence in SARS-CoV-2 infected vs uninfected, power calculations are based on the null hypothesis that there is no difference between individuals with and without SARS-CoV-2 in the outcome rate.

The assumptions used to generate these power calculations include both elements outside the study’s team’s control (e.g., baseline outcome rate in individuals without SARS-CoV-2) as well as elements amenable to changes in study design (e.g., individuals with SARS-CoV-2 strata group size).  Assumptions include:

- 3,600 individuals with SARS-CoV-2 and 1,200 individuals without SARS-CoV-2
- Baseline outcome rate in individuals without SARS-CoV-2: 2.5% with the contingency that the baseline outcome rate may vary between age strata (18-40 years, 41-64 years, ≥ 65 years)
- Outcome rate in individuals with SARS-CoV-2: presented as scenarios based on absolute or relative differences from baseline outcome rate in individuals without SARS-CoV-2. Also presented under the likely scenario that outcome rates vary between age strata
- Alpha = 0.05 (fixed)

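### The sensitivity analysis that gives missing covariates their own category leaves residual confounding in the SARS-CoV-2 comparison, so it is a misleading check on robustness

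*Protocol*

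**What the plan says.** Protocol section 3.4.1 describes the design: "This is a prospective, observational study without an intervention". Sections 2.3 and 3.2 make symptomatic people who test negative the controls for those who test positive.

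Section 3.9.1 plans to report the risk of ME/CFS and other conditions "in those with versus without SARS-CoV-2 infection as risk difference or risk ratios or odds ratios, as appropriate", and to "adjust for additional patient-level factors of interest, including age, sex, race/ethnicity, income, and presence of specific underlying conditions".

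On missing data the same section has three sentences. The first sets out the general approach: "Multiple imputation will be considered to handle missing covariate and outcome data in these analyses". The second names the imputation technique, which is chained equations for every incomplete variable. The third fixes the check on robustness: "Sensitivity analyses will be conducted using missing categories for covariates and including only people with non-missing outcome information".

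The last can be read as one analysis with both features or as two separate analyses. The point is the same either way, and it concerns only the covariate part. The protocol states no assumption under which missing categories would control confounding, and gives no caution about reading the result.

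**The concern.** In a randomised comparison a missing-category term does little harm, because baseline covariates are unrelated to treatment by design. Here infection status may be related to income, race/ethnicity, underlying conditions and the other listed factors, which is the reason for adjusting at all.

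For a person whose income, say, is unknown, the missing category records only that it is unknown. Among all such people, positives and negatives are compared without regard to income. The fitted coefficient for infection then blends an income-adjusted contrast from those with data and an income-unadjusted one from those without.

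A sensitivity analysis for missing data should change an assumption about the missing values. This one also changes how much confounding is removed. If it disagrees with the imputed result, that may be an artefact of weaker adjustment. If it agrees, that is little evidence that the imputation is sound.

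**Working it through.** **1. The plan's own figure.** Section 3.8 gives "3,600 individuals with SARS-CoV-2 and 1,200 individuals without SARS-CoV-2", a 2.5% rate in negatives, a 2.5-point difference and alpha 0.05. I take alpha as two-sided.

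- Pooled rate = (0.025 × 1,200 + 0.05 × 3,600) / 4,800 = 0.04375.
- Null SE = √[0.04375 × 0.95625 × (1/1,200 + 1/3,600)] = 0.00682.
- Alternative SE = √[0.025 × 0.975/1,200 + 0.05 × 0.95/3,600] = 0.00579.
- Power = Φ[(0.025 − 1.96 × 0.00682)/0.00579] = Φ(2.01) = 97.8%.

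This matches the protocol and is not in dispute. The same rates give an odds ratio of (0.05/0.95)/(0.025/0.975) = 2.05, used in step 4.

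**2. Inputs for the bias check.** From the protocol: 75% positive, and 2.5% risk in negatives. Assumed, because the protocol gives none of them: binary confounders present in 35% of positives and 20% of negatives, independent of each other given infection status; their odds ratios for the outcome; and values missing completely at random, independently across covariates. The true infection odds ratio is set to 1.00. Logistic models were fitted to the exact population tables, so there is no simulation error.

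Hand check of the unadjusted odds ratio, using the rare-outcome approximation [1 + (OR − 1) × 0.35] / [1 + (OR − 1) × 0.20] per confounder:

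- One confounder, OR 3: 1.70/1.40 = 1.21.
- Three confounders, OR 2: (1.35/1.20)³ = 1.42.

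**3. Results, true odds ratio 1.00.**

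| Setting | Missing per covariate | Unadjusted | Missing category | Complete covariates |
|---|---|---|---|---|
| Three confounders, OR 2 | 5% | 1.42 | 1.02 | 1.00 |
| same | 10% | 1.42 | 1.04 | 1.00 |
| same | 20% | 1.42 | 1.08 | 1.00 |
| same | 30% | 1.42 | 1.12 | 1.00 |
| same | 40% | 1.42 | 1.16 | 1.00 |
| Same, prevalences reversed | 30% | 0.71 | 0.90 | 1.00 |
| One confounder, OR 3 | 30% | 1.21 | 1.06 | 1.00 |

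The share of confounding left in, on the log scale, is close to the missing fraction. For three confounders at 30% missing it is ln 1.115 / ln 1.416 = 0.31, using unrounded odds ratios.

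**4. Different inputs, true odds ratio 2.05.** One confounder with 30% prevalence, confounder–infection OR 0.5 to 3, confounder–outcome OR 3 to 5:

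- 20% missing completely at random: missing-category odds ratio 1.94 to 2.23.
- 40% missing completely at random: 1.84 to 2.42.
- 30% missing in negatives and 10% in positives: 1.92 to 2.28.
- Covariate unrelated to infection, in these same three missingness settings: 2.04 to 2.05, so essentially no bias.

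Complete-covariate analysis gives 2.05 in all of these. If missingness depends on both infection status and outcome (about 16% missing overall), it gives 2.23, and the missing-category fit gives 2.48 to 3.60 when the covariate is a confounder.

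**5. Bias against precision.** With 30 events in 1,200 and 180 in 3,600, the SE of the log odds ratio is √(1/30 + 1/1,170 + 1/180 + 1/3,420) = 0.20. The bias at 30% missing, three confounders, is ln 1.12 = 0.11, or about 0.6 SE. At 10% missing it is ln 1.04 = 0.04, about 0.2 SE.

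**6. Price of complete covariates.** Three covariates each 30% missing leave 0.7³ = 34%, about 1,650 of 4,800. The SE rises to 0.20/√0.343 = 0.34.

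**The case against.** The strongest reply is that this is a secondary analysis, the bias is modest, and the replacement may do worse overall. With three confounders each 30% missing, root mean squared error on the log scale is √(0.20² + 0.11²) = 0.23 for missing categories, against about 0.34 for complete covariates. Complete-covariate analysis also fails when missingness depends on infection and outcome together. That is plausible for underlying conditions, because the participant timeline in section 3.14 marks them at follow-up and not at enrolment. Heavy missingness is unlikely for age, which determines eligibility.

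All of this stands, and it limits both the weight of the point and the remedy. It does not rescue the missing-category analysis as a robustness check: a tighter interval around a partly confounded estimate does not show whether the imputation can be trusted. Where complete-covariate analysis was biased in step 4, missing categories were further from the truth.

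A reader might infer stronger points that the document does not support:

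- *That the missing-category figure could become the reported result*, since imputation is only to be considered. The very next sentence says "Chained equations will be used to impute each variable with missing data", and the missing-category fit is labelled a sensitivity analysis. Nothing makes it a fallback for the main estimate.
- *That all confounding is uncontrolled in the affected participants.* Only the covariate they lack is unadjusted; those recorded for them still are.
- *That the estimate is biased whatever the covariate.* It must relate to both infection status and outcome.

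**Conclusion.** The point holds in a limited form. For any incompletely recorded covariate that is a true confounder, the missing-category analysis gives a biased positive-versus-negative estimate even when values are missing completely at random. The direction depends on how the confounder is distributed between the groups, so the analysis is not reliably conservative.

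Under the assumed three-confounder inputs the bias grows from about 2–4% on the odds-ratio scale at 5–10% missing to about 16% at 40%. These sizes depend wholly on assumed prevalences, odds ratios and missing fractions. What does not depend on them is that the method fails to remove confounding by a covariate in those who lack it.

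The consequence is a robustness check that can mislead. The main estimate and the power figure are untouched. This is worth correcting, but it is not a major defect.

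**What to change.** In Protocol section 3.9.1, for the SARS-CoV-2 positive-versus-negative estimates, replace the missing-category wording with text such as:

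> *A sensitivity analysis will be restricted to participants with complete data on the adjustment covariates, and its result will be compared with that from imputation by chained equations.*

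The part of the sentence on non-missing outcomes can stay. A total ban on missing categories is not needed. If such a result is still shown, label it as not fully controlled for confounding and do not use it to judge robustness.

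The change is one sentence and needs no new data. The cost is fewer participants and wider intervals, possibly much wider if several covariates are often missing (step 6). The complete-covariate result should itself be read with care, because it is biased if missingness depends on both infection status and outcome. Reporting the number and percentage missing for each covariate, by test result, would let readers judge how far either problem applies.

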## 3.6. Data collection

### 3.6.1. Trial procedures and evaluations

Results for a SARS-CoV-2 viral test (i.e., nucleic acid amplification test or antigen test) are confirmed by the research staff either through visualizing the result in the EMR or by reviewing an image of the test result sent to the research staff by the participant. After an eligible patient enrolls in the study, a combination of self-reported information and information generated from the patient’s own health information is connected to the Hugo platform, collected, and sent to the study site over the 18-month follow-up period (Appendix A).

Self-reported data: Using Hugo, surveys including the variables outlined above are sent by electronic mail or text to participants at the research site every 3 months throughout the follow-up period. These responses are sent through the Hugo platform and then shared with the study team. Subjects use their personal smartphone, tablet, computer, or other electronic device to connect to the internet and answer surveys that ascertain their symptoms, health care use, health care experience, and physical, mental, and social health over an 18-month period. Responses sent by participants are encrypted. To minimize participant burden, each data collection episode is designed to take approximately 15 minutes or less to complete.

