Patient-Centric Data Sharing: Participants connect their own health system portal account with the Hugo platform at enrollment (Figure 1). Hugo is a web-based platform used to longitudinally collect data for this study. The Hugo platform gives patients the ability to collect and maintain their personal health records in a centralized, cloud-based account. Participants will create a Hugo account and connect the health system portal accounts they choose to connect with the Hugo platform. This may include patient portals from healthcare systems, pharmacies, laboratories, and insurers. Individuals direct Hugo to share their health records with the research team according to the terms in the informed consent. This information is sent from Hugo to the research analytic core and stored in accordance with their institutional policies. The specific portal-related information available through Hugo in use for INSPIRE includes hospital and clinical patient portals yielding current data on medications, appointments and visits, test orders and results, clinical notes, problems, diagnoses, vital signs, demographics, and immunizations. After the study, participants can maintain their Hugo account or opt to delete their account and data.

Participants can connect their health system(s) portal accounts with Hugo at set up but may need assistance if they have technical issues or if they do not complete this initial step at enrollment. Once participants create an account in Hugo and link their portals, no additional actions are required to stream data into Hugo. Technical support from the enrolling site or clinical core is provided to resolve any difficulties setting up an account.

During the study, periodically Hugo downloads identifiable data outlined in the IRB protocol and consent form. Research sites have access to site-specific dashboards to track enrollment, identify which data sources are connected, and to monitor survey responses. Deidentified, individual-level data are sent from Hugo to the analytic team periodically for quality assurance and analysis.

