## 3.11. Data monitoring

### 3.11.1. Interim analysis

Periodic reports of de-identified data from participants at each site are exported from the Hugo data management system for monitoring and analysis by the study cores. These data will be used to monitor the adequacy of recruitment, with due consideration to the balance of subjects with positive versus negative tests as well as their age distribution, and completeness of follow-up questionnaires.

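### For survey outcomes, the one named sensitivity analysis for missing outcomes (complete case) does not test the missing-at-random assumption of the planned imputation

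*Protocol*

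**What the plan says.** Protocol section 3.9.1 sets out the handling of missing data in three sentences.

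- Main approach: "Multiple imputation will be considered to handle missing covariate and outcome data in these analyses". The engine follows: "Chained equations will be used to impute each variable with missing data". No imputation variables are listed.
- Check for covariates: "Sensitivity analyses will be conducted using missing categories for covariates".
- Check for outcomes: a further analysis "including only people with non-missing outcome information", that is, complete case.

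The patient-reported outcomes come from remote surveys sent "every 3 months throughout the follow-up period" (section 3.6.1), with data "sent to the study site over the 18-month follow-up period". EMR data arrive differently: once a participant has linked a portal, "no additional actions are required to stream data into Hugo" (section 3.6.1). Section 3.5 takes hospitalization, hospital-free survival and ICU-free survival from the EMR. Section 3.11.1 monitors "completeness of follow-up questionnaires", which tracks the amount of missing data but does not analyse its effect.

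**The concern.** A sensitivity analysis should vary the assumption that the main analysis cannot verify. For imputation by chained equations as normally run, that assumption is that response is explained by observed data (missing at random). Complete case does not relax it. It needs response to be unrelated to the outcome given the covariates in the analysis model, which is no weaker.

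The study is open to this problem. Participants can know their test result, there is no masking, and they must keep answering voluntary questionnaires for 18 months. Response could plausibly depend on both test group and current health. If it does, the comparison of test-positive with test-negative participants is biased, and two analyses that share the bias may agree and be read as robust.

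The protocol also has a resource that it does not assign to this purpose. A linked participant who stops answering may still supply visits, diagnoses and hospitalizations. For survey outcomes, complete case leaves that person out.

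**Working it through.** **1. The plan's own figure.** The protocol gives no figure on non-response. Its one power figure for the full sample (section 3.8) is 97.8% for a 2.5-point difference with 3,600 vs 1,200. With 5.0% vs 2.5%, two-sided alpha 0.05, pooled variance and no continuity correction, I get 97.78%. The same pooled test is used in step 4.

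**2. What each named analysis assumes about a missing survey outcome.**

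- Chained-equation imputation: response depends only on variables in the imputation model.
- Complete case: response is unrelated to the outcome given the covariates in the analysis model.
- Response that depends on the unseen outcome: allowed by neither.

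**3. Can the contrast between the two show the bias?** I used a large-sample simulation (2 million people, 75% test-positive). The outcome is a T-score with SD 10 and a true difference of -3.0. An EMR marker correlates 0.7 with post-baseline health. About 69% respond. In the first two rows less healthy test-positives respond less; in the third this holds in both groups. All these settings are assumptions.

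| Response depends on | Complete case | Imputation without EMR | Imputation with EMR |
|---|---|---|---|
| EMR-visible health, test-positives only | -1.9 | -1.9 | -3.0 |
| The outcome itself, test-positives only | -1.4 | -1.4 | -2.2 |
| The outcome itself, equally in both groups | -3.0 | -3.0 | -3.0 |

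Without EMR data the two named analyses agree on the same wrong answer. With EMR data in the imputation, the contrast exposes the part of the bias that the EMR explains. It does not remove the rest.

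**4. Possible size for a binary outcome.** With true risk p, response r1 among those with the outcome and r0 among those without, the complete-case risk is

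p·r1 / (p·r1 + (1 − p)·r0).

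Assume the same true risk in both groups, r0 = 0.65, and no outcome-related selection in controls. Responders are taken as 65% of 3,600 and of 1,200, so 2,340 and 780. The rejection probability is Φ((d − 1.96·s0)/s1) + Φ((−d − 1.96·s0)/s1). Here d is the difference in complete-case risks, s0 its pooled and s1 its unpooled standard error.

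Worked case, p = 5% and r1 = 0.80:

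- Test-positive risk: 0.040 / (0.040 + 0.6175) = 6.08%. Control risk: 5.00%. Risk ratio 1.22.
- d = 0.0108, s0 = 0.00967, s1 = 0.00924.
- (0.0108 − 0.0190)/0.00924 is about -0.88, so the first term is 0.190. The second is below 0.001. The total is 19%.

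| Response, test-positives with vs without outcome | Risk ratio at 5% | False-positive chance at 5% | False-positive chance at 2.5% |
|---|---|---|---|
| 50% vs 65% | 0.78 | 28% | 18% |
| 70% vs 65% | 1.07 | 6% | 6% |
| 80% vs 65% | 1.22 | 19% | 11% |
| 90% vs 65% | 1.36 | 42% | 23% |

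The 2.5% column uses the baseline rate in section 3.8. At that rate the risk ratio for 80% vs 65% is again 1.22, from 0.020 / (0.020 + 0.63375) = 3.06% against 2.50%.

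**5. Dependence on the controls.** Keep p = 5% and 80% vs 65% in test-positives, and let controls with the outcome also respond more often than 65%:

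- at 70%: risk ratio 1.13, false-positive chance 11%;
- at 75%: 1.06 and 6%;
- at 80%: 1.00 and 5%.

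**The case against.** **This belongs in the SAP.** Tipping-point analyses, auxiliary variables and response tables often sit in an SAP, which is not shown here and may contain them. Nothing in section 3.9.1 rules out further analyses. This is the strongest objection, and it limits the point to what the protocol fixes. But the protocol does name a check for missing outcomes, and the named check does not examine the assumption at issue. That is a choice of method, not a detail left open.

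**A reader might infer that the named analyses can never reveal dropout bias.** The protocol does not support that. It also mentions imputing outcomes, and if that imputation is done and includes EMR data, its contrast with complete case can show EMR-explained bias (-3.0 vs -1.9 in step 3). The protocol commits to neither condition.

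**A reader might infer that EMR data are discarded in general.** They are not. EMR-derived outcomes are not made missing by survey dropout. The loss concerns survey outcomes only. EMR data stream only for participants who linked a portal, and section 3.6.1 recognises that some do not complete this step at enrollment.

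**A reader might infer that the bias inflates the COVID-19 effect.** The protocol gives no basis for a direction, nor for assuming that controls are free of selection. Controls are also symptomatic and receive the same surveys and incentive. Sicker test-positives could stay or leave, and equal selection in both groups leaves the risk ratio close to its true value.

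**Conclusion.** The point holds for survey outcomes. Complete case is the only sensitivity analysis that the protocol names for missing outcomes, and it does not test the missing-at-random assumption of the imputation it accompanies. Agreement between the two would be weak evidence of robustness, above all if the imputation leaves out the EMR data.

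The size is unknown because the protocol gives no response rates. In the assumed scenarios the risk ratio under no true effect runs from 0.78 to 1.36. The false-positive chance runs from 6% to 42% at a 5% rate and from 6% to 23% at 2.5%. It returns to the nominal 5% when controls are selected in the same way. These figures show that differential response of moderate size could matter; they do not predict that it will occur. The point is worth acting on, but it does not undermine the EMR-derived outcomes or the design.

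**What to change.** In protocol section 3.9.1, for survey outcomes:

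1. State that the imputation model includes EMR utilisation and diagnoses, for participants with linked portals, and earlier survey scores as auxiliary variables.
2. Add a delta-adjusted (missing-not-at-random) imputation. Set the shift separately for test-positive and test-negative participants, and run it in both directions to the point where the conclusion changes.
3. Keep complete case as a secondary, descriptive result.
4. Report survey response by test group and by last observed health status.

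This needs statistical programming only, with no new data and no further contact with participants. The downside is modestly more analysis and a conclusion that may have to be stated less firmly.

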## 3.14. Participant timeline

Figure 1. Participant Timeline

|  | Enrolment | Post-enrollment |  |  |  |  |  | Close-out |
| --- | --- | --- | --- | --- | --- | --- | --- | --- |
| TIMEPOINT | 0 | 3 mos. | 6 mos. | 9 mos. | 12 mos. | 15 mos. | 18 mos. | tx |
| ENROLLMENT: |  |  |  |  |  |  |  |  |
| Eligibility screen | X |  |  |  |  |  |  |  |
| Informed consent | X |  |  |  |  |  |  |  |
| ASSESSMENTS: |  |  |  |  |  |  |  |  |
| Age, gender, symptoms of SARS-COV-2 infection, recent health care use, social determinants of health | X |  |  |  |  |  |  |  |
| Outpatient visit, emergency department visit, hospitalization, intensive care stay, death, physical and mental health (PROMIS-29), cognitive SF-8, hospital-free survival, intensive care-free survival, dyspnea, cough, exercise, social determinants of health, work and activity status, myalgic encephalomyelitis/chronic fatigue syndrome |  | X | X | X | X | X | X | X |
| Preexisting conditions |  | X | X | X | X |  |  | X |

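### Prior health care use is not among the named adjustment factors, so the comparison of later use by SARS-CoV-2 status could be confounded by pre-illness care habits

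*Protocol*

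**What the plan says.** Protocol section 3.9.1 plans this comparison by test result: "Characterize health care utilization (ambulatory and ED visits, hospitalizations, post-acute care, telehealth visits) among SARS-CoV-2 positive participants by age and compare these to SARS-CoV-2 negative". The models it lists for such outcomes are logistic regression for binary events and "Poisson or Cox regression for count data (e.g., number of hospitalizations over time").

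A later paragraph of the same section, after a sentence on the risk of ME/CFS and other health conditions, says: "We will also adjust for additional patient-level factors of interest, including age, sex, race/ethnicity, income, and presence of specific underlying conditions such as hypertension"; diabetes is its other example. It then adds that "additional covariates of interest available from electronic record data will be assessed for their association with adverse outcomes".

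Two sources of earlier health care use exist. Figure 1 (section 3.14) has an enrolment-only row reading "Age, gender, symptoms of SARS-COV-2 infection, recent health care use, social determinants of health". Section 3.6.1 describes linked portals "yielding current data on medications, appointments and visits, test orders and results", among other items. The protocol states neither a look-back window for the enrolment item nor a depth of history for the portals. Table 1 allows enrolment up to 42 days after the test.

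**The concern.** Past use of health care is a natural predictor of later use. Age, income and diagnoses are only partial stand-ins for it. The two groups are defined by a test result, not by randomisation. Recruitment runs through record screening, publicity with self-enrolment, and outreach using testing-agency contacts, in a mix that differs by site (section 3.3). Nothing in the design makes habitual care use equal in positives and negatives.

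If it is unequal, a habit that predates the illness would be read as an effect of SARS-CoV-2 on later visits and admissions, or would hide one. The protocol collects information that could guard against this but does not commit to using it in this comparison.

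**Working it through.** **1. The protocol's own figure.** Inputs from section 3.8: 3,600 positives, 1,200 negatives, alpha 0.05 (sidedness is not stated; two-sided reproduces the result), 2.5% vs 5.0%. Two-proportion z test, pooled variance under the null and unpooled under the alternative:

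- pooled rate = (1,200 × 0.025 + 3,600 × 0.05) / 4,800 = 0.04375
- SE under the null = √[0.04375 × 0.95625 × (1/1,200 + 1/3,600)] = 0.006818
- SE under the alternative = √[0.025 × 0.975/1,200 + 0.05 × 0.95/3,600] = 0.005789
- power = Φ[(0.025 − 1.96 × 0.006818) / 0.005789] = 97.8%, as stated.

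The same method gives 69.6% for the 7% vs 5% comparison in Table 4 at full enrolment. These rates are not specific to any outcome; they are used here only as a yardstick.

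**2. Bias if prior use is left out.** The protocol gives no prior-use data, so these inputs are assumptions. Let a and b be the shares of prior heavy users among positives and negatives, and k their relative risk of later use. With a true ratio of 1.00, the apparent ratio is [1 + a(k − 1)] / [1 + b(k − 1)]. The imbalance must be read as what remains after the named covariates.

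| Positives / negatives | k = 2 | k = 3 |
|---|---|---|
| 20% / 20% | 1.00 | 1.00 |
| 20% / 25% | 1.20/1.25 = 0.96 | 1.40/1.50 = 0.93 |
| 20% / 30% | 1.20/1.30 = 0.92 | 1.40/1.60 = 0.88 |
| 30% / 20% | 1.30/1.20 = 1.08 | 1.60/1.40 = 1.14 |

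At 20% / 30%, a true 7% vs 5% would be tested as if the positive rate were 7% × 0.923 or 7% × 0.875. Power falls from 69.6% to 45% or 29%.

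A simulated Poisson model with robust standard errors (300 runs, 3,600 vs 1,200, gamma frailty, true ratio 1) agrees. Unadjusted ratios were 0.96 (20%/25%, k = 2), 0.92 (20%/30%, k = 2) and 0.88 (20%/30%, k = 3). The null was rejected in about 10%, 33% and 62% of runs, against 5% nominal. Adjusting for heavy use brought the ratio back to about 1.00 each time.

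**3. Precision.** For a binary heavy-use indicator with share a, and event rate p, the correlation with the event is ρ = (k − 1) × p₀ × √[a(1 − a)] / √[p(1 − p)], where p₀ = p / [1 + a(k − 1)].

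- a = 0.20, k = 2, p = 0.05: p₀ = 0.0417, ρ = 0.08
- a = 0.30, k = 3, p = 0.07: p₀ = 0.0438, ρ = 0.16

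Multiplying both variances by 1 − ρ², a linear-model approximation, moves power for 7% vs 5% from 69.6% to 69.9% (ρ = 0.08) or 70.8% (ρ = 0.16). In the simulation with equal shares and k = 3, the standard error fell from 0.058 to 0.055, about 5%.

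**The case against.** The strongest reply is that no covariate set is fixed for the utilization models. The named factors follow the sentence on ME/CFS and other health conditions, the list is introduced as illustrative, further record-based covariates are foreseen, and a statistical analysis plan that is not shown may settle the matter. This largely stands. A reader might infer that the protocol excludes prior use; it does not. What remains is that the only factors it names omit it. The sentence on further covariates speaks of their association with outcomes, not of controlling the comparison by test result.

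Second, both groups are symptomatic people who sought or received a test, recruited by the same routes, and no passage shows that their prior use differs. This also stands. A reader might infer that heavy users in either group are enough to cause bias; with equal shares the bias is nil. The residual imbalance is a possibility, not a documented fact.

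Third, a reader might expect a large gain in power. A correlation of 0.5 would raise 69.6% to 82.1%, but the heavy-user scenario above implies only 0.08 to 0.16. At an event rate of 6.5%, even if every event fell in heavy users, the correlation could not exceed 0.53 (20% heavy users) or 0.40 (30%).

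Fourth, the enrolment item may include care for the index illness, since enrolment can follow the test by up to 42 days and takes in hospitalised patients. Such care is partly a result of infection, and adjusting for it could remove part of the effect. It is therefore defensible not to adjust for the item as recorded. This does not remove the concern, but it determines how the covariate must be defined.

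**Conclusion.** The point holds as an improvement to the planned analysis. The protocol compares later health care use between non-randomised groups, collects information on earlier use, and names adjustment factors without it. If pre-illness use differs by test result beyond what age, sex, race/ethnicity, income and underlying conditions capture, the comparison is confounded.

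The size and direction cannot be known from the protocol. Under the assumed 10-point imbalance and a relative risk of 2 to 3, the ratio is off by about 8% to 14% in either direction (0.92 to 0.88, or 1.08 to 1.14); a 5-point imbalance gives 0.96 to 0.93. Precision is a secondary reason, worth about one power point or less for 7% vs 5% with a binary heavy-use covariate. No figure stated in the protocol is wrong on this account.

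**What to change.** In section 3.9.1, state that models comparing ambulatory, ED, hospital, post-acute and telehealth use by SARS-CoV-2 status adjust for health care use of the same type in a fixed window before symptom onset or the index test.

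- **Source:** portal visits dated within the window. Use the enrolment item only where it can be dated to before the illness.
- **Exclusion:** leave care for the index illness out of the covariate.
- **Zero versus missing:** a linked portal that covers the window and shows no visits counts as zero use. Only participants without usable pre-illness data are missing; imputing visits for genuine non-users would misclassify the confounder.
- **Missing values:** use the chained-equation imputation or the missing-category approach that section 3.9.1 already mentions.
- **Sensitivity analysis:** report the model with the currently named covariates alongside.

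The cost is a few sentences of analysis text and some derivation work, with no new participants or surveys. The downside is that pre-illness use will be missing for some participants, because the protocol does not say how far back portal records reach.
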